#### Secondary outcome measures

Secondary outcomes at 8 and 12 months postrandomisation will be compared between the intervention and control groups using a mixed effects linear regression model as for the primary outcome. A 95% CI for the mean difference in this parameter between the treatment groups will also be calculated together with the associated p value.

Outcome measures for the participating supporters at 8 months will be compared between the intervention and control groups using a mixed effects linear regression model. The mean difference in outcome with associated 95% CI and p value will be presented for: (1) the baseline (specific to the secondary outcome) and site adjusted analysis and (2) adjusted analysis with additional covariates in addition to (1).

#### Subgroup analysis

A subgroup analysis using a mixed effect linear regression model, with the primary outcome (DEMQOL) at 8 months postrandomisation as the response will be carried out. We will use an interaction statistical test between the randomised intervention group and subgroup to directly examine the strength of evidence for the treatment difference between the treatment groups varying between subgroups. Supporter involvement (yes or no) will be the only a priori defined subgroups to be considered for interaction test.

### Health economics evaluation

A trial-based economic evaluation will be undertaken of an ITT comparison of the costs and outcomes of the two trial arms. A cost-effectiveness analysis will be undertaken of the incremental cost per QALYs of the JtD intervention compared with usual care provided through NHS memory services. QALYs will be calculated using the EQ-5D-5L preference-based index administered at baseline, 8 and 12 months. A sensitivity analysis will be undertaken using utility values from the DEMQOL-U, which can be derived from responses to the DEMQOL questionnaire.^30^ The total cost of the intervention will be estimated at the individual participant level and will include the costs of providing the intervention and the subsequent consequences for the use of routine health and social care services. The average cost per attendance will be calculated and this estimate will be applied to the actual number of group and individual sessions that each participant attended.

The use of services by trial participants will be collected in detail using a HSCRU questionnaire administered at 8 and 12 months postrandomisation. Service use will be costed using the most recent National Reference Cost Data and Unit Costs of Health and Social Care.^49 50^ Missing data will be dealt with using multiple imputation for EQ-5D-5L, DEMQOL-U and resource use data.^51^ A random effects linear regression model, accounting for clustering, will be fitted, and the model will include baseline scores for EQ-5D-5L and baseline costs. The central analysis of mean incremental costs per QALY will be subjected to a full sensitivity analysis of key parameters including the measure used to estimate QALYs and number of participants at the weekly sessions. A full probabilistic sensitivity analysis will be performed to examine the probability of cost-effectiveness of the intervention for the NHS for different levels of costs and QALY gains.^52^

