**Methods and analysis:**

The RCT is a pragmatic, two-arm, parallel group trial designed to test the clinical and cost-effectiveness of JtD compared with usual care. Recruitment will be through NHS services, third sector organisations and Join Dementia Research. The sample size is 486 randomised (243 to usual care and 243 to the intervention usual care). Participants can choose to ask a friend or relative (supporter) to become involved in the study. The primary outcome measure for participants is Dementia-Related Quality of Life (DEMQOL), collected at baseline and at 8 months’ postrandomisation. Secondary outcome measures will be collected from participants and supporters at those visits. Participants will also be followed up at 12 months’ postrandomisation with a reduced set of measures. A process evaluation will be conducted through qualitative and fidelity substudies. Analyses will compare the two arms of the trial on an intention to treat as allocated basis. The primary analyses will compare the mean DEMQOL scores of the participants at 8 months between the two study arms. A cost-effectiveness analysis will consider the incremental cost per Quality Adjusted Life Years of the intervention compared with usual care. Qualitative and fidelity substudies will be analysed through framework analysis and fidelity assessment tools respectively.

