### Randomisation, blinding and bias

To minimise bias, allocation will be concealed through the use of a centralised web-based randomisation service. The randomisation sequence will be stratified by delivery site and constrained by a fixed block size to ensure participants are allocated evenly to each arm of the trial at each delivery site. Participants will be randomised in equal numbers to intervention and control arms. An unblind member of the research team who will not be conducting outcome assessments will enter the participants’ details into the randomisation system and inform the relevant parties of the outcome.

Members of the Trial Steering Committee (TSC), study statisticians, health economists and outcome assessors will be blinded to treatment allocation while the trial is ongoing. For practical reasons linked to the provision of a centralised web-based randomisation service and the setup and delivery of the intervention groups, some members of the research team will not be blinded, including the Trial Manager and Chief Investigator. Due to the nature of the intervention, participants will not be blinded. If the outcome assessors know (or suspect) they have been unblinded, this will be recorded on an unblinding form.

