### Site selection and participant recruitment

The JtD trial will operate in England within 13 NHS trusts with specialist dementia services. The sites will be selected based on a convenience sample of locations clustered geographically around the north and midlands (for a list of sites, see study ISRCTN webpage^26^).

Previous studies involving persons with dementia have shown that recruiting participants to such studies can be challenging.^27^ To ensure sufficient numbers are recruited to the study, a number of recruitment pathways will be used: referral from clinical teams; mail-outs to eligible patients via primary or secondary care clinical teams; study promotion via posters and so on; third sector organisations and the Join Dementia Research database. The research team will contact interested participants and send further information about the study. Clinical teams will check with the potential participants that they are willing to be approached by the research team before an approach is made.

To enable potential participants to make a direct approach to the research team, a reply card will be designed which can be completed, sealed and returned to the central research team who will then pass the information on to relevant local site researchers. These reply cards will be distributed with information sheets at events including dementia cafes or posted as part of mail-outs to General Practitioners (GPs). Local promotions, for example, via posters in clinics or GPs, will include the telephone and email details of local researchers for direct contact to take place.

A consent and eligibility visit will be arranged if an individual would like to take part where trained researchers will assess eligibility and request written informed consent.

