### Data analysis

As JtD is a pragmatic parallel group randomised trial, with a usual care (control) arm, data will be reported and presented according to a revised CONSORT statement.^44^ Statistical analysis will be performed on an ITT basis. All exploratory tests will be two-tailed with alpha=0.05. Baseline demographics and quality of life data will be described and summarised overall and by treatment group.

The primary analysis will compare mean patient reported DEMQOL scores at 8 months postrandomisation between the intervention (JtD) arm and control arms using a mixed effects linear regression model adjusted for DEMQOL baseline score and site and allowing for the clustering of the outcome by the JtD intervention.^45–47^ The trial is a partially nested design with comparison of a group therapy (JtD) with individual therapy with clustering in one (intervention) arm. Each person with dementia in the control group (unclustered arm) will be treated as a cluster (singleton) of size one. The cluster indicator will be treated as a random effect. A stratification variable used for randomisation (site) will be included as a fixed factor.^48^ A partially clustered mixed effects linear regression model with homoscedastic errors as well as a heteroscedasticity mixed effects linear regression model will also be considered to account for potential differential variability of outcomes between the two treatment groups. A 95% CI for the mean difference in DEMQOL scores between the intervention and control groups will be calculated together with the associated p value. A further adjusted analysis may also be performed depending on the observed degree of imbalance in baseline covariates (which are of potential prognostic importance) again using a mixed effects linear regression model. Additional covariates (of potential prognostic importance) include other baseline variables, such as age, gender, PHQ-9 and GAD-7. In the event that there are more than 10 couples (20 participants) living under the same roof from different households in the study, then the primary and secondary analyses will be changed to take into account the hierarchical or clustered nature of the data. A multilevel mixed effects model will be used; the random effects will be JtD intervention groups (top level) and couple/singles (lower level). Individual participants who are not part of a couple will be treated as clusters of size one.

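### As stated, the cost-effectiveness regression does not name site, the randomisation stratum, so its standard errors would be conservatively too wide; the baseline covariate for the DEMQOL-U sensitivity analysis should also be stated

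*Protocol article*

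**What the plan says.** The economic model is described in one sentence of the Health economics evaluation section: "A random effects linear regression model, accounting for clustering, will be fitted, and the model will include baseline scores for EQ-5D-5L and baseline costs". The section does not refer back to the clinical model.

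On allocation, Randomisation, blinding and bias says: "The randomisation sequence will be stratified by delivery site and constrained by a fixed block size". On the clinical primary model, Data analysis says: "A stratification variable used for randomisation (site) will be included as a fixed factor". Secondary outcome measures analyses participants' secondary outcomes in the same way as the primary outcome. For supporters it specifies adjustment for site and for each outcome's own baseline.

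On the utility measure, EQ-5D-5L at baseline, 8 and 12 months gives the main QALY. The section then adds: "A sensitivity analysis will be undertaken using utility values from the DEMQOL-U, which can be derived from responses to the DEMQOL questionnaire". Table 1 shows DEMQOL collected from participants at baseline, 8 and 12 months.

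**The concern.** Stratified randomisation removes between-site differences from the treatment contrast. An analysis gets the benefit only if its model recognises the strata. The clinical model does so; the economic model, as described, does not say that it does.

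The clustering makes this matter more than usual. JtD groups sit inside sites and control participants are singletons. Without a site term, two JtD groups differ partly because their sites differ, and the model reads that difference as group-to-group variation in the intervention arm. The standard error of the arm difference then includes variation that the design has already balanced out. It feeds into the uncertainty around incremental cost and QALYs, and so into the probability of cost-effectiveness. Cost-effectiveness is part of the trial's primary aim.

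The secondary question is the baseline covariate when QALYs come from DEMQOL-U. The only utility baseline named is EQ-5D-5L. A chance difference between arms in baseline DEMQOL-U enters the QALY directly, and adjusting for a different instrument removes only part of it.

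**Working it through.** **Plan's own figures.** The article gives no figure for the economic regression. Its sample size section supplies the inputs, and these reproduce:
- Unadjusted: 2 × (1.96 + 1.2816)² × (11/4)² = 158.9, so 159 per arm (stated 160).
- Design effect: 1 + (8 − 1) × 0.03 = 1.21, and 160 × 1.21 = 193.6, so 194.
- Loss to follow-up: 194/0.8 = 242.5, so 243.

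**Site: set-up.** With 194 per arm in groups of 8 there are about 24 JtD groups. The check used 12 sites with two groups of 8 each (192 per arm), group variance 0.03, and site plus residual variance summing to 1. The site share ρ is assumed.

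**Site: hand check.**
- With site in the model: variance = 0.03/24 + 2(1 − ρ)/192.
- Without site: the JtD arm contributes [0.03 + ρ + (1 − ρ)/8]/24. The control arm contributes the pooled residual/192, where the pooled residual is [168(1 − ρ) + 191]/359. The weights 168 = 24 × 7 and 191 are the within-group and control degrees of freedom.

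| ρ | Variance with site | Variance without site | SE ratio |
|---|---|---|---|
| 0.02 | 0.01146 | 0.00719 + 0.00516 = 0.01235 | 1.04 |
| 0.05 | 0.01115 | 0.00828 + 0.00509 = 0.01337 | 1.10 |
| 0.10 | 0.01063 | 0.01010 + 0.00496 = 0.01507 | 1.19 |

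**Site: simulation.** The partially nested REML model was fitted to 600 simulated trials per value of ρ.

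| ρ | Mean SE without / with site | Ratio | Power without / with site |
|---|---|---|---|
| 0.02 | 0.1105 / 0.1073 | 1.03 | 88.2% / 88.7% |
| 0.05 | 0.1150 / 0.1058 | 1.09 | 86.8% / 91.2% |
| 0.10 | 0.1207 / 0.1032 | 1.17 | 79.3% / 89.3% |

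The hand check runs slightly higher because it treats groups at the same site as independent and takes the root of a mean variance. A separate run of 400 trials gave 2.7%, 8.5% and 16.3%. The point estimates had the same spread under both models, so the wider standard error is not real uncertainty.

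A simpler formula, 1/√(1 − ρ), gives 1.0%, 2.6% and 5.4%. It applies to a model with no group random effect, so it understates the effect when clustering is by JtD group.

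**What this does to the output.** Take, for illustration, a true probability of cost-effectiveness of 90%, that is, net benefit 1.2816 standard errors above zero. Dividing 1.2816 by 1.03, 1.09 and 1.17 gives about 89%, 88% and 86%.

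**DEMQOL-U.** Trapezoid weights for visits at 0, 8 and 12 months are (8/12)/2 = 1/3, (8/12)/2 + (4/12)/2 = 1/2, and (4/12)/2 = 1/6. Assume equal SDs and a correlation of 0.5 between visits:
- Var(QALY) = 1/9 + 1/4 + 1/36 + 2 × 0.5 × (1/6 + 1/18 + 1/12) = 0.694.
- Cov(QALY, baseline) = 1/3 + 0.5 × (1/2 + 1/6) = 0.667.
- r = 0.667/√0.694 = 0.80.
- Residual share adjusting for own baseline: 1 − 0.64 = 0.36.
- Residual share adjusting for EQ-5D-5L, if it correlates 0.5 with baseline DEMQOL-U and predicts the QALY only through it: 1 − (0.80 × 0.5)² = 0.84.
- SE ratio = √(0.84/0.36) = 1.53.

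The ratio runs from 1.29 to 2.07 over visit correlations of 0.4 to 0.7 and cross-instrument correlations of 0.3 to 0.7. Setting r directly, with cross-instrument correlation 0 to 0.5, gives 1.04–1.05 at r = 0.3, 1.12–1.15 at r = 0.5 and 1.31–1.40 at r = 0.7.

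For imbalance, with 194 per arm and an assumed SD of 0.10 to 0.20, a 1.96-SE baseline difference is 1.96 × SD × √(2/194) = 0.020 to 0.040. One third of that, 0.007 to 0.013 QALY, enters the QALY difference through the baseline term alone.

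**The case against.** The strongest reply is that the article is a condensed account. The sentence says what the model will include, not that nothing else enters, and a full protocol or health economics analysis plan may already list site. This stands in part: a reader might infer that site has been left out, and the text does not establish that. But the article does more than stay silent. It sets out a separate economic model with named covariates and no link to the clinical model, and those covariates differ from the article's own practice elsewhere.

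The random effects are also undefined. If site were one of them, or if the economic model followed the clinical one, most of the problem would go. That is a reason to state it, because the 3% to 17% range assumes clustering by JtD group.

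A reader might infer that the base-case result is biased. It is not: blocked allocation within site balances site between arms, and the error is conservative.

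A reader might also infer that DEMQOL-U QALYs will be adjusted for EQ-5D-5L alone, with a large loss of power. The documents do not say so. The covariate sentence can be read as describing the main EQ-5D-5L analysis, with the baseline changing when the measure does. There is also no power target for a DEMQOL-U QALY difference, so a loss from 90% would be hypothetical.

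Finally, the check used 12 sites, while the article says: "The JtD trial will operate in England within 13 NHS trusts with specialist dementia services". This does not alter the argument.

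The quoted sentence raises a separate matter that this point does not resolve. It calls for baseline costs, but on resource use the section says: "The use of services by trial participants will be collected in detail using a HSCRU questionnaire administered at 8 and 12 months postrandomisation". The source of baseline costs needs to be reconciled with that schedule.

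**Conclusion.** The point holds as a precision issue. If the economic regressions are fitted as stated, with JtD-group clustering and no site term, the standard errors of incremental cost and QALYs are too wide by about 3%, 9% and 17% at site intracluster correlations of 0.02, 0.05 and 0.10. With the SE ratios above, a nominal 5% test would run at roughly 4.4%, 3.3% and 2.2% (twice the normal tail beyond 1.96 × ratio). The site correlations are assumptions. At the low end the effect is small, and at every value the estimate itself is unaffected.

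The DEMQOL-U point is a request for a clear statement. Baseline EQ-5D-5L is a partial substitute at best. The loss from relying on it ranges from about 4% to about 107% in the standard error across the assumptions tried, which include equal SDs and an EQ-5D-5L effect only through DEMQOL-U. It concerns a sensitivity analysis; the main QALY analysis already names its own baseline utility.

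**What to change.** In the health economics analysis plan, before database lock:
- Add site as a fixed factor to both the cost and the QALY regressions, as in the clinical primary model, and name the clustering unit. With 13 trusts as the sites this takes 13 − 1 = 12 degrees of freedom, out of about 388 participants with outcome data.
- State that the QALY regression adjusts for the baseline value of the utility being analysed: EQ-5D-5L in the main analysis and DEMQOL-U in the DEMQOL-U sensitivity analysis.

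No new data are needed, because baseline DEMQOL-U is scored from the DEMQOL questionnaires already collected. If the full plan already contains both terms, confirming this is enough.

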### Process evaluation

The process evaluation has been designed to: (1) examine the factors that may influence the fidelity of intervention delivery and (2) explore its perceived impact and acceptability from user and provider perspectives. There are two strands to this, the fidelity assessment and qualitative interviews, explained below.

#### Fidelity assessment

The fidelity of intervention delivery as well as of the training and supervision received by facilitators will be assessed on the basis of criteria derived from the intervention protocol and manual. Fidelity checks will adhere to a framework based on that identified by the Behaviour Change Consortium^23^ and NICE guidance on behaviour change.^24^ The fidelity assessment framework (adapted from Bellg *et al* 2004^23^) will assess and monitor for the consistency, facilitator training (in terms of standardised delivery of training and skills acquisition for facilitators), intervention delivery (in terms of standardised delivery between intervention groups) and the receipt of the intervention by intervention group participants.

Training delivery and receipt of the facilitator training will be observed and rated by the same two researchers (the lead for fidelity and one other member of the research team) for inter-rater reliability using a bespoke *Training observation checklist*. To assess facilitator adherence to the manualised intervention and participant receipt of the intervention, a purposive selection of group meetings across sites will also be observed using a *Group observation checklist* which is based on the contents of the intervention and the training. Each selected group will be observed on two occasions to identify facilitator drift or changes in participant behaviour.

Frequencies will be used to determine the extent to which the training programme received by facilitators maintained fidelity to what was intended. Data will also be analysed to compare intervention delivery between and across sites to check for consistency. Inter-rater reliability between coders will be determined using the Kappa statistic.^53^ Similar methods have been used in previous studies.^54^

#### Qualitative interviews

An embedded qualitative substudy will explore the mechanisms of the intervention, for example, what elements of the intervention appear to support people to improve their self-management and well-being and what promotes good facilitation of the intervention.

Individual qualitative semistructured interviews will be conducted with a purposive sample of 20 participants (approximately 10%) from the intervention groups observed in the fidelity substudy and with approximately 12 participating supporters, preferably supporters of participants who are also being interviewed. A participant interview schedule and supporter interview schedule will be developed to cover the following themes:

Range and nature of issues that influence experiences of taking part in the intervention.Factors that may influence the effectiveness, adoption and diffusion of this innovation in the future.Perceived skills and competencies required to facilitate the intervention.The barriers and facilitators to uptake and continued use.The effect of the intervention on living with dementia.The effect of the intervention on the experiences of supporting someone with dementia.

Semistructured interviews will also be conducted with approximately 20% of all facilitators and supervisors across the sites on completion of their delivery of the intervention. The sample will include a range of sites and facilitators with different levels of experience of delivering the intervention. A facilitator interview schedule and supervisor interview schedule will be created to cover the following themes:

What issues promote the effectiveness of intervention facilitation.The skills and competencies required to facilitate the programme.The barriers and facilitators to its uptake and continued use.Factors that may mediate or moderate the effectiveness of the intervention.

Researchers undertaking participant interviews will be trained to use enhanced methods of communication with people with dementia to try to ensure that meaningful discussion takes place. Transcripts of interviews will undergo respondent validation.

